## Abstract

**Background:**

Endometrial fibrosis caused by intrauterine adhesion (IUA) can lead to hypomenorrhea, amenorrhea, and even infertility and abortion. The postoperative recurrence rate of severe IUA remains high, giving rise to low pregnancy rates. An extracellular matrix (ECM) scaffold, a new biological material that can promote cell proliferation and differentiation at lesions, has been widely used in general surgery and neurosurgery. The present study applied ECM scaffolds in obstetrics and gynecology for the first time to improve endometrial fibrosis, repair severe IUA, and improve pregnancy outcomes for infertile patients.

**Methods:**

This paper presents a prospective randomized single-blind controlled superiority study of infertile women aged ≤40 years with IUA. According to the scoring criteria for IUA established by the American Fertility Society, patients with moderate or severe IUA were randomized into two groups at a ratio of 1:1; patients in the experimental group were treated with an ECM scaffold (small intestinal submucosa [SIS]) + intrauterine balloon, while patients in the control group were treated with an intrauterine balloon only. A hysteroscopic examination of adhesion repair was performed again after 2 months of postoperative hormone replacement therapy. Endometrial tissue was sampled during the two operations, and immunohistochemistry was used to observe endometrial and microvascular proliferation. After thawing and resuscitation, a postoperative frozen embryo transfer was performed on the participants in both groups, and their endometrial thickness, intrauterine volume, endometrial vascularization flow index, endometrial flow index, and uterine artery blood flow resistance were evaluated by 3D ultrasonography. The rates of embryo implantation, clinical pregnancy, and early spontaneous abortion were observed.

**Discussion:**

The ECM scaffold (SIS) + intrauterine balloon method was able to repair endometrial fibrosis and improve IUA. This new technique represents a novel treatment method for improving the pregnancy outcome of infertile patients with moderate/severe IUA.

**Trial registration:**

Chinese Clinical Trial Register ChiCTR2100052027. Registered on October 14, 2021.

## Background

Infertility affects 48.5 million couples worldwide with a prevalence estimated at 3.5–16.7% in low- and middle-income countries and up to 30–40% in sub-Saharan Africa [1]. Intrauterine adhesion (IUA) accounts for 8% of the causes of infertility and is also a common cause of secondary infertility [2]. Two-thirds of female infertility cases are caused by repeated embryo implantation failure (RIF) during in vitro fertilization–embryo transfer as a result of endometrial factors, indicating the serious impact of an endometrial injury on female reproductive function [3].

In addition to infertility, an endometrial basal layer injury can also lead to partial or total intrauterine occlusion, resulting in amenorrhea, hypomenorrhea, periodic abdominalgia, recurrent abortion, placental abnormalities, and other symptoms. Accordingly, endometrial injury has become a major reproductive system disease that seriously threatens female reproductive health.

Endometrial injury can easily cause IUA, which primarily manifests as an endometrial basal layer injury caused by trauma, infection, and other factors, resulting in the dysfunction of functional endometrial repair; in turn, this will lead to the proliferation of fibrous connective tissue and endometrial fibrosis as well as partial or total intrauterine occlusion [2, 4]. According to the consensus of Chinese experts on the clinical diagnosis and treatment of intrauterine adhesions [5], at present, for patients suffering from infertility, recurrent abortion, and oligomenorrhea and for those with special fertility requirements, transcervical resection of adhesion (TCRA) can be conducted as a preferred treatment (recommendation level: C). Moreover, TCRA combined with an intrauterine device (IUD), Foley balloon support, or estrogen and progesterone replacement therapy has shown degrees of anti-adhesion value, although their effects are variable. An IUD placement after moderate and severe IUA could reduce the formation rate of re-adhesion to 35% [6] (evidence level: I). But meta-analysis showed that the menstrual improvement rate ranged between 28.5 and 100%. Several studies have indicated significant differences in this regard [7]. In addition, although an intrauterine balloon can make the total effective rate of IUA repair reach 71.67% [8] and improve the menstrual rate up to 81.4–95% [9, 10], the shape of the balloon used in clinics is not suitable for the intrauterine cavity, which makes it difficult to block the wound completely. Moreover, if the intrauterine balloon is not placed properly, intimal ischemia and necrosis may occur, which will impact intimal regeneration and repair. In particular, for patients with severe IUA, due to endometrial basal layer damage, reduced residual normal endometrial tissue, and poor regeneration ability, the recurrence rate of postoperative adhesion can still be as high as 62.5%, while the success rate of pregnancy will range between only 22.5 and 33.3% [11]. Therefore, establishing an anti-adhesion method that can promote the repair of endometrial injury is of great significance.

Advances in the field of tissue engineering present new opportunities in the development of regenerative medicine and provide new directions for the treatment of endometrial injuries. As a new medical material, the primary structure of a biological patch comprises an extracellular matrix (ECM) fibrous scaffold made up of collagen, elastic fiber, glycoprotein, laminin, and proteoglycan; together, these proteins provide an ideal scaffold for the repair of defective tissue. In recent years, the effect and feasibility of using biological patches to strengthen and repair fascia tissue in pelvic floor reconstruction have been confirmed [12]. The present authors’ research applied an ECM scaffold to repair endometrial injuries in a rat model and increase the pregnancy rate among rats [13]. The results were consistent with the effect of small intestinal submucosa (SIS), as reported by Ho, in the repair of vaginal injury in a rat model [14].

This paper proposes a new scheme for the prevention of IUA and endometrial repair. An ECM scaffold (i.e., SIS, provided by Cook Inc., USA) was placed, based on TCRA, and combined with an intrauterine balloon to explore the effect of the ECM scaffold on endometrial cell proliferation and anti-fibrosis and analyze its efficiency in improving the clinical pregnancy outcomes of patients with moderate and severe IUA infertility.

### Experimental design

The current paper presents a prospective randomized single-blind controlled superiority study that evaluated the ability of ECM scaffolds in the repair of endometrial fibrosis. Patients with infertility with a history of secondary hypomenorrhea, a thin endometrium, and RIF (excluding factors such as embryo quality) who suffered from IUA were recruited from the Reproductive Medicine Center of Shanghai Changzheng Hospital, China. According to the scoring criteria for IUAs established by the American Fertility Society (AFS) shown in Table 1 [15], patients with moderate or severe IUAs were randomized into the ECM scaffold + intrauterine balloon implantation group or the intrauterine balloon implantation group at a ratio of 1:1. The study design process is shown in Fig. 1.

**Table 1 Tab1:** AFS scoring criteria for intrauterine adhesion (1988)

Category	Score
Extent of intrauterine adhesion	
<1/3	1
1/3–2/3	2
>2/3	4
Type of adhesion	
Filmy	1
Filmy and dense	2
Dense	4
Menstrual pattern	
Normal	0
Hypomenorrhea	2
Amenorrhea	4

Total AFS score = score for extent of cavity involved + score for type of adhesion + score for menstrual pattern

severe: 9–12 points; moderate: 5–8 points; mild: 1–4 points

*AFS* American Fertility Society

**Fig. 1 Fig1:**
[figure not shown]
Study design flowchart

### Evaluation criteria

The evaluation criteria for inclusion in the protocol were as follows.Secondary hypomenorrhea: The menstrual blood volume was less than 20 ml or had decreased by 1/3 of the original menstrual blood volume, and the menstrual cycle length was less than 3 days if the previous menstrual bleeding duration and volume had been normal. Patients could calculate this according to the number of sanitary napkins they had used.Diagnosis of infertility: Patients who failed to become pregnant successfully with a normal sex life without taking contraceptive measures for more than 1 year.A “thin endometrium” meant that the thickness of the endometrium was less than the threshold thickness for becoming pregnant. Currently, there is no unified standard for this threshold. Most scholars posit that an endometrial thickness of <7 mm as measured by transvaginal ultrasound on the day of human chorionic gonadotropin (hCG) could be considered a thin endometrium [16].An IUA diagnosis under 3D ultrasound [17] in which type I indicates a clear endometrium and a discontinuous endometrial line, type II denotes a mild intrauterine separation with a separation diameter less than 1 cm, type III refers to an unclear endometrium with a thickness of less than 0.2 cm that is not demarcated from the surrounding muscle layer, and type IV involves severe intrauterine separation with a separation diameter greater than 1 cm. A diagnosis could be made if one of the above characteristics was present.“Repeated embryo implantation failure” refers to failure to achieve a pregnancy following 2–6 IVF cycles, in which more than 10 high-grade embryos were transferred into the uterus [18].

The protocol complies with the principles of the Declaration of Helsinki as well as Good Clinical Practice (GCP) guidelines. The hospital’s ethics committee approved the study protocol. The trial was registered in the Chinese Clinical Trial Registry.

The inclusion criteria were as follows:Patients aged ≤ 40 yearsPatients with a body mass index = 18–27.9 kg/m^2^Patients with secondary decreased menstruationPatients with a thin endometriumPatients with RIFPatients who met the diagnostic criteria of the World Health Organization for infertility (normal regular sex life, no contraception, no pregnancy for 1 year)Patients who had undergone in vitro fertilization (IVF)/intracytoplasmic sperm injection (ICSI) treatment cycle and obtained at least two high-quality embryos (including fallopian tube factors, ovulation disorders, male severe oligozoospermia, severe asthenospermia, and severe teratospermia)Patients with a clinical diagnosis of moderate/severe IUA (conforming to the AFS 1988 classification criteria) [15]Patients who agreed to undergo hysteroscopy and postoperative re-examinationPatients who were able to understand and cooperate in the clinical study process and comply with the requirements of the study protocols until its completionPatients who agreed to be included in the clinical study and who voluntarily provided written informed consent accordingly

The exclusion criteria were as follows:Patients with irregular vaginal bleeding of an unknown causePatients with ovarian, pituitary, or hypothalamic amenorrheaPatients with abnormal uterine developmentPatients with uterine fibroids of >2 cm, adenomyosis, or severe pelvic endometriosisPatients with a history of malignant or borderline tumorsPatients with breast hyperplasia or other related diseasesPatients with a history of pelvic tuberculosis or acute infection of the genitourinary systemPatients with serious cardiovascular, cerebrovascular, respiratory, or digestive diseasesPatients with a history or family history of severe thrombotic diseasesPatients with severe liver or kidney dysfunction or immune system disordersPatients with psychosis or a serious mental illnessPatients with other diseases that were incompatible with human-assisted reproductive technologyPatients with a history of allergic reactions to porcine-derived productsPatients who could not accept porcine-derived materials due to religious beliefs or ethnicityOther patients who were considered ineligible for the study

The withdrawal criteria were as follows:The participant or their legal guardian voluntarily requested withdrawalViolation of the inclusion/exclusion criteriaWithdrawal in the case of other unexplained serious complicationsWithdrawal from the study in the case of becoming pregnant during the treatmentThe sponsor of the study proposed discontinuing the study for safety reasonsSubjects whose participation in this study was discontinued by the hospital’s ethics committeeSubjects whom investigators considered unsuitable for participation in the study

### Screening of infertility patients with intrauterine adhesions

Patients with infertility with secondary hypomenorrhea were evaluated by 3D ultrasound for endometrial thickness and morphology on days 3–7 after menstruation, and the intrauterine volume, endometrial vascularization flow index (VFI), endometrial flow index (FI), and endometrial vascularization index (VI) were recorded. According to the patients’ medical history and 3D ultrasound imaging examinations, infertile women aged ≤ 40 years who suffered from IUAs were screened and admitted to the hospital for adhesiolysis. Following admission, the patients were collected for a review of their general circumstances and medical history, which included blood pressure, heart rate, pulse and respiration, menstruation, menstrual and obstetrical histories, past medical history, operation history, and family medical history.

### Study protocols

#### Hysteroscopic evaluation

Following perfect preoperative preparation and the provision of signed consent, the hysteroscopy-guided separation of IUAs was performed under general anesthesia 3–7 days after the end of menstruation. During the surgery, the bladder lithotomy position of the patient was taken. A hysteroscopy operating mirror (Storz, Germany) (dimensions: 5.5–7.5 mm) equipped with hysteroscopic direct-vision micro scissors was used; the normal saline perfusion system continued to expand the uterus at a pressure of 120–140 mmHg, and the cervix was expanded by 5.5–7.5 mm. The hysteroscopy was performed with IUA having been scored before surgery. Cooled knife-sharp separation was used in all of the surgeries, with difficult procedures being performed under the guidance of B-scan ultrasonography. The success criteria were to remove scar tissue, preserve normal intima, normal or basically normal morphology of uterine cavity, and clear display of bilateral fallopian tube openings. For severe intrauterine adhesion, B-ultrasound should be used to monitor the thickness of uterine myometrium during operation to prevent uterine perforation.

Based on the AFS scoring criteria for IUA [15] (Table 1), patients with moderate/severe IUA were randomized into the experimental group (which included the placement of an ECM scaffold [SIS] and a Foley balloon) or the control group (which included the placement of a Foley balloon) at a ratio of 1:1. In the control group, the Foley balloon was placed after surgery, and normal saline was injected into the balloon according to the size of the uterine cavity. When obvious resistance occurred, the saline injection was stopped (normal saline was 3~5 ml); a drainage bag was connected, and the balloon was removed after 5 days (the recommended prevention time of the balloon by experts in China was 5~7 days [5], recommendation level C). To reduce the infection rate among the patients, a 5-day balloon retention time was implemented in combination with the actual situation of our hospital. Antibiotics were used to prevent any infections from occurring after surgery. In the experimental group, the ECM patch was cut into a 2 × 5-cm rectangle. Fold the patch in half along the midpoint line of the short side, then open it, and place the unfilled balloon on the fold line. Cover the other half of the patch on the balloon, wrap it tightly, clamp it with long curved forceps, and place it into the uterine cavity. Other procedures were the same as those in the control group.

#### Postoperative hormone replacement therapy

Patients in the experimental and control groups all received anti-infection treatment following surgery. Additionally, 2-mg exogenous estrogen (twice daily) and 50-mg aspirin (once daily) were given for 14 consecutive days (starting on the first day after surgery), and 10-mg dydrogesterone (twice daily) was added on day 10 after commencing estrogen therapy. Postoperative hormone replacement therapy (HRT) was provided in two cycles.

#### Hysteroscopic re-examination

Patients in both the experimental and control groups received a hysteroscopic re-examination 3–7 days after the end of the second menstruation to evaluate the IUA repair. Postoperative HRT was repeated (the same as stated above). According to the evaluation standard for uterine cavity repair, if the second hysteroscopy showed that uterine cavity adhesion had not been recovered (i.e., there was no obvious change between the uterine cavity’s shape and that before separation, based on hysteroscopy), or the adhesion was more serious, full adhesiolysis was performed again, and additional anti-adhesion methods, such as inserting an IUD and replacing estrogen and progesterone for one month, were implemented.

#### Tissue repair evaluation

An endometrial biopsy was performed following IUA lysis. A small amount of endometrial tissue was taken for pathological and endometrial repair evaluations. The degree of endometrial fibrosis and the number of proliferating cells and microvessels in the two groups were observed using Masson’s staining and immunohistochemistry techniques to evaluate the effect of the ECM scaffolds on the proliferation of endometrial cells. A transmission electron microscope was used to observe the ultrastructure of the endometrial cells.

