##### Determination of endometrial cell proliferation

To determine whether the ECM could promote endometrial cell proliferation, Ki67 immunohistochemical staining was conducted. Von Willebrand factor immunohistochemical staining in the endometrial injury region was conducted to observe the regeneration and distribution of microvessels in the endometrium. At a magnification of ×40, the proliferative cell count of three fields was randomly selected and averaged.

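### Biopsy after lysis makes a weak fibrosis baseline, the second-look sample is not clearly protected from repeat lysis, and a raw Ki67 count mixes cell density with proliferation

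*Protocol article*

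**What the plan says.** Five places in the protocol article bear on this point.

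- Tissue repair evaluation: "An endometrial biopsy was performed following IUA lysis". The tissue is used to compare fibrosis (Masson's staining), proliferating cells and microvessels between the two groups. The section does not say which operation is meant.
- Hysteroscopic evaluation, on what lysis aims to do: "The success criteria were to remove scar tissue, preserve normal intima, normal or basically normal morphology of uterine cavity".
- Abstract, Methods, on when tissue is taken: "Endometrial tissue was sampled during the two operations".
- Hysteroscopic re-examination: both groups "received a hysteroscopic re-examination 3–7 days after the end of the second menstruation to evaluate the IUA repair". If the cavity has not recovered, or the adhesion is worse, "full adhesiolysis was performed again".
- Determination of endometrial cell proliferation: Ki67 is the marker, and at ×40 "the proliferative cell count of three fields was randomly selected and averaged". No total-cell or area denominator is given. The injury region is named for the von Willebrand factor (vWF) stain only.

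Experimental design gives repair of endometrial fibrosis as what the study evaluates. Neither Primary outcome measures nor Secondary outcome measures lists the histology.

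**The concern.** Histology is the only direct measure of fibrosis in the article; the AFS score grades the extent and type of adhesion and the menstrual pattern. Three features weaken the histology as a measure of repair.

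1. The first sample is taken after the step that removes scar. It comes from selected tissue and probably shows less fibrosis than the woman had on entry.
2. If the same order applies at second look, scar is cut out before sampling only in women who have done badly. That acts after randomisation and depends on outcome, so randomisation does not balance it.
3. A raw count of positive cells rises when a field holds more cells, even if the share of cells that are dividing is unchanged.

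At stake is whether the trial could support a statement that the scaffold repairs fibrosis or stimulates proliferation, as opposed to a statement about AFS response.

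**Working it through.** The plan gives no effect size, standard deviation or power for fibrosis or Ki67, so there is no figure to reproduce. All numbers in steps 2 and 4 are assumptions chosen to show direction, apart from the 83 per arm, which is in Sample size.

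**Step 1. Order of events at the first operation.** Hysteroscopic evaluation makes scar removal part of successful lysis; Tissue repair evaluation places the biopsy after lysis. The first sample is therefore drawn from what remains. The text does not say how much fibrosis remains.

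**Step 2. What an understated baseline does.** Assume true baseline fibrosis of 60 (SD 10) in both arms, a mean fall of 10 in control and 18 with the scaffold, and a first sample that records a share *k* of true baseline. Second-look means are 60 − 10 = 50 (control) and 60 − 18 = 42 (scaffold).

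| | *k* = 1.0 | *k* = 0.3 |
|---|---|---|
| Recorded baseline | 60 | 0.3 × 60 = 18 |
| Change, control | 50 − 60 = −10 | 50 − 18 = +32 |
| Change, scaffold | 42 − 60 = −18 | 42 − 18 = +24 |
| Between-arm difference in change | −18 − (−10) = −8 | 24 − 32 = −8 |
| Between-arm difference at second look | 42 − 50 = −8 | 42 − 50 = −8 |

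A simulation with 83 per arm and 5,000 repeats agreed: about −8.0 for both between-arm differences at either *k*, and a scaffold-arm change of −18.0 or +24.0. The within-arm change is corrupted; the between-arm contrast is not. This result assumes the same *k* in both arms, a second-look sample from every woman, and no effect of repeat lysis on that sample.

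**Step 3. What repeat lysis before the second sample would do.** For each arm let *M* be the true mean fibrosis at second look, *r* the share re-lysed, *F* the mean fibrosis in those women, and *k* now the share of fibrosis left after repeat lysis. The observed arm mean is *M* − *r*(1 − *k*)*F*. With S for scaffold and C for control:

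observed difference = (M_S − M_C) + (1 − *k*)(r_C F_C − r_S F_S).

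If the scaffold works, the first term is negative. With more women re-lysed in the control arm and fibrosis in those women no lower there, the second term is positive. The contrast moves towards zero. The documents give no re-lysis rate, so this can be signed but not sized.

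**Step 4. Raw Ki67 count.** Count = cells per field × labelling index.

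- Same index, different density: 200 × 0.20 = 40 and 300 × 0.20 = 60. The count rises by half with no change in proliferation.
- Different index, different density: 300 × 0.20 = 60 and 200 × 0.30 = 60. A higher index is hidden.

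The Discussion describes the matrix as helping cells migrate to lesions. On that mechanism the scaffold could raise cell density without raising the index. Randomisation does not remove the ambiguity, because density may itself be a treatment effect.

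**The case against.** The strongest reply is that the stated comparison is between two randomised groups, that tissue is taken at both operations, and that the second look falls in the same window in both arms. No section names a before-to-after change as the analysis. This stands, and step 2 supports it: an understated baseline alone leaves the between-arm contrast intact. A reader might infer that neither stain can show anything about repair. The documents do not support that.

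The Discussion also holds that fibrosis in severe disease does not improve when the cavity is restored. So lysis need not leave tissue free of fibrosis, and understatement of the baseline is probable but not proven complete.

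A reader might further infer that only women who fail are biopsied at second look, because only they are lysed again. The Abstract speaks of sampling at both operations without that limit, and the timing phrase may refer to the first lysis only. Nor can the number affected be taken from the repair rates in Sample size: effective repair is an AFS fall of at least 4 points, whereas repeat lysis is triggered more narrowly, by no obvious change in cavity shape or by worse adhesion. A woman who improves by less than 4 points fails the endpoint but need not be re-lysed.

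On Ki67, the plan says it counts proliferating cells, and a count can differ between randomised arms. Laboratory detail may also sit in the full protocol or the operating procedures. That limits the criticism, but the article does state a count as the readout, and a count cannot separate density from proliferation.

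**Conclusion.** The point holds in a limited form. The first-operation sample is probably a poor fibrosis baseline, so within-arm change is not reliable evidence of repair. The second-look comparison between arms is sound only if every woman is sampled before any repeat lysis; sampling after it would pull the fibrosis contrast towards no difference, by an amount the documents do not allow one to estimate. A between-arm difference in the raw Ki67 count could reflect cell density alone.

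The conclusions on order rest on reading the biopsy and lysis sections as written. The numbers are illustrations on assumed values. Priority is modest: histology is in neither outcome list and no sample size is tied to it, though it bears directly on the stated aim of repairing fibrosis.

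**What to change.** - Reconcile the Abstract, Hysteroscopic re-examination and Tissue repair evaluation so that tissue is sampled from every participant at both hysteroscopies: before scissor work where the site is accessible, always before any repeat lysis, and from a recorded site.
- State that the fibrosis conclusion rests on the between-arm comparison at second look, not on within-arm change.
- Report Ki67 as positive nuclei divided by all nuclei on the same fields. Report Masson collagen and vWF-stained vessels per unit area of tissue.

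The main cost is somewhat longer image reading on fields already taken; no new stain is needed. If the Abstract's account is right and tissue is already taken at both operations in all women, no biopsy is added and only the order changes. If second-look sampling is at present confined to women who are re-lysed, the change would add biopsies in the others, which is a further reason to settle the wording.
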